### Phase II: pilot implementation of the intervention

#### Sampling strategy

The District Education Officers (DEOs) will provide a list of mixed-sex secondary schools from two districts in Mwanza region (as agreed on in the formative phase). A shortlisting will be conducted based on student enrolment (targeting mid-sized schools enrolling between 125 and 140 girls in Forms 2 and 3), location (to include both urban and peri-urban schools), proximity to Mwanza city, and both day and boarding mixed-sex schools where possible. A random sample of four schools will be obtained from the shortlisted schools.

In each school, all girls in Forms 2 and 3 who assent to participate and a random sample of 50 male students enrolled in the same classes as the girls, will be invited to join a longitudinal cohort study, within which we will administer a pre and post intervention assisted self-completed paper-based survey (as described above). We determined that 500 girls—each participating in the baseline and end line survey—were required to provide 80% power to detect a difference of 0.075 points in the Menstrual Practice Needs Scale (MPNS-36) questionnaire assuming a total MPNS mean score of 1.82 (SD 0.37) at baseline^22^; a two-tailed test at 5% significance level; and allowing for an intracluster correlation of 0.05% and 20% loss to follow-up between baseline and end line surveys.

In addition, we will obtain a random sample of 10 girls in each school from the participants in the female cohort who reported in the baseline questionnaire to have missed two or more days of school during and because of their last menstruation to qualitatively assess changes in school participations and experiences of the intervention. We will also purposively select two staff in each school based on individual involvement in MSRH issues within the school to participate in KIIs (see table 1 for more details).

No participants will receive monetary incentives. All will receive MSRH education and workbooks; girls will receive a kit containing, among other things, a reusable menstrual product.

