12	Students in pilot schools	Phase II: Pilot study, Mwanza	Observations of Femme teaching sessions (n=10 with girls, n=8 with boys)	160 girls and 160 boys (based on ~20 per class),	We aim to observe 4 first sessions, 4 second sessions and 2 8-week check sessions for girls, we will then observe 2 boys sessions per school. We will randomly select 2 of the schools to observe the 6–8 week check in sessions. The observer will introduce themselves as part of the external process evaluation team. No names will be documented on the observation forms.	MSRH knowledge Engagement/participation in the sessions Fidelity to the intervention intended contents
13	Teachers in pilot schools	Phase II: Pilot study, Mwanza	Observation of Femme sessions with teachers	20 teachers (5 per school)	We will randomly select 2 of the schools to observe the teacher sessions. The observer will introduce themselves as part of the external process evaluation team. No names will be documented on the observation forms	Acceptability Fidelity Engagement and participation in the sessions
14	Parents of students in pilot schools	Phase II: Pilot study, Mwanza	Observation of Femme— school-led parents meetings	~200–500	The external evaluation team (MITU) will attend and observe any Femme-school meetings—1 in each school. The observer will introduce themselves as part of the external process evaluation team. No names will be documented on the observation forms.	**Acceptability of the intervention** Engagement strategies —how Femme engages with the parents and with the school. Opportunities and barriers for uptake and school project ownership.
15	Students in pilot schools	Phase II: Pilot study, Mwanza	Repeated IDIs	20 girls (5 from each school)	During the full class meeting when we introduce the study, we explain how we are wanting to conduct additional data collection (as well as the questionnaire) with a smaller sample of girls to better document their experiences. We will randomly select a subsample of girls who reported in the baseline questionnaire to have missed two or more schools days during and because of their last menstrual period We will invite these girls into a IDI (without disclosing the selection process, they will be able to do this themselves if they are comfortable) The IDIs will take place post baseline and endline survey	Ability to manage pain Self-efficacy in the management of menstruation School and social participation

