**Figure 3 F3:**
[figure not shown]
Flow chart of the PASS MHW intervention pilot study illustrating the intervention and evaluation activities.

Qualitatively, we will conduct 20 sequential in-depth interviews at three time points (before, immediately post intervention, 12 months later) with five girls from each school, who reported in the baseline questionnaire, to have missed school for two or more days during and because of their last menstruation. The aim of these sequentialin depth interviews (IDIs) is to assess any changes in participation and to explore if/how the intervention may have impacted on the girls’ ability to participate in school. We will also conduct KIIs with two staff per school to assess MSRH knowledge among staff overseeing student’s MSRH issues while in school. All interviews and FGDs will be conducted in Swahili by a trained female research assistant accompanied by a note taker and recorded using digital voice recorders.

We will assess one primary and eight secondary outcomes. The data collection tools for each outcome are described in table 2.

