(3) Sequential IDIs with 20 girls who (at baseline) reported to have missed two or more days of school during and because of their last menstrual period who will be interviewed at three time points.

(4) Four schools—baseline and endline assessment.

*Data sources.

WASH, water, sanitation and hygiene.

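### The sequential-interview sample and schedule are stated inconsistently, and choosing girls on one high absence report means regression to the mean will tend to look like benefit

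*Protocol article*

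**What the plan says.** **Number of girls.** The Phase II sampling strategy takes "a random sample of 10 girls in each school from the participants in the female cohort", restricted to those reporting at least two missed school days at the last period. Table 1, row 15, gives "20 girls (5 from each school" under the same restriction. The outcome evaluation section describes "20 sequential in-depth interviews at three time points (before, immediately post intervention, 12 months later) with five girls from each school", and Table 2, footnote (3), also has 20 girls.

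**Interview times.** Table 1, row 15, says: "The IDIs will take place post baseline and endline survey". The outcome evaluation section names three occasions, and Table 2, footnote (3), refers to girls "who will be interviewed at three time points".

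**Use.** The outcome evaluation section says that the aim of the interviews "is to assess any changes in participation and to explore if/how the intervention may have impacted" on girls' ability to take part in school. Table 2 lists the interviews as a data source for secondary outcome 6 (school and social participation), next to eight survey questions put to all girls. In the interviews the girls describe what they missed at the last menstrual period, days included. The strengths and limitations list discloses that there is no control group and no randomisation. It does not mention regression to the mean.

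**The concern.** There are two separate problems.

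The first is that the study team cannot follow all the stated versions. The population, the selection rule and the purpose are the same wherever these interviews appear, so the different figures are not describing different sub-studies. Workload, transcription and costs depend on which version is used.

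The second is how change in these girls would be read. They enter because one self-report, about one period, was at or above a cut-off. Some of them will have had an unusually bad month. At a later period such girls will on average report less absence even if nothing has been done. The same quantity is asked about again, change in it is linked to the programme, and no comparison group shows what would have happened anyway. A girl chosen after a bad period may sincerely credit the programme for an ordinary one.

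**Working it through.** **1. Number of girls.** The sampling strategy fixes the number of schools: "A random sample of four schools will be obtained from the shortlisted schools".

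- Table 1, outcome evaluation and Table 2: 5 × 4 = 20. This reproduces the stated total of 20.
- Sampling strategy: 10 × 4 = 40, twice that total.

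**2. Interview times and workload.** Table 1 gives two occasions. The outcome evaluation section and the Table 2 footnote give three.

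| Girls | 2 occasions | 3 occasions |
|---|---|---|
| 20 | 40 interviews | 60 interviews |
| 40 | 80 interviews | 120 interviews |

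**3. Which occasion Table 1 lacks.** Girls are picked from their baseline survey answers, so any interview before the intervention has to follow the baseline survey. Table 1, row 8, places that survey before implementation. The post-baseline interview in Table 1 is therefore most naturally the pre-intervention interview of the outcome evaluation section. The occasion missing from Table 1 is the one immediately after the intervention.

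**4. Regression to the mean, threshold model.** Assume that the tendency to miss days is normal at each period, with correlation *r* between two periods and no intervention effect. Let *p* be the share of girls meeting the two-day rule and *t* the matching cut-off. The share of selected girls who qualify again is P(X₂ > t | X₁ > t) = P(X₁ > t, X₂ > t) / p. The article gives neither *p* nor *r*, so both are assumptions.

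| r | p = 10% | p = 20% | p = 30% | No longer qualify |
|---|---|---|---|---|
| 0.3 | 0.22 | 0.33 | 0.43 | 57-78% |
| 0.5 | 0.32 | 0.44 | 0.52 | 48-68% |
| 0.7 | 0.47 | 0.57 | 0.64 | 36-53% |
| 0.9 | 0.69 | 0.75 | 0.79 | 21-31% |

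Example for p = 10% and r = 0.5: the joint probability is 0.0324, and 0.0324 / 0.10 = 0.32, so 68% would no longer qualify. Over r = 0.3-0.7 the range is 36-78%.

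**5. Second check with counts of days.** Days missed were simulated as binomial over five school days, with a girl-specific probability drawn from a beta distribution and no intervention effect. The cohort means were 0.5, 1.0 and 1.5 days, and the correlation between two counts was 0.55 to 0.95. All of these are assumptions. The results agree with E[follow-up | selected] = μ + r × (baseline mean of selected − μ).

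| Cohort mean | r | Selected, baseline | Selected, later | Fall |
|---|---|---|---|---|
| 0.5 | 0.56 | 2.53 | 1.63 | 36% |
| 1.0 | 0.77 | 3.12 | 2.63 | 16% |
| 1.5 | 0.95 | 4.32 | 4.18 | 3% |

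First row by formula: 0.5 + 0.56 × (2.53 − 0.5) = 1.64, against 1.63 simulated. Over all scenarios, mean days missed in selected girls fell by 3-36%, and 7-51% no longer met the rule. The mean of the whole cohort did not change in any scenario.

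**The case against.** The strongest reply is that this component is qualitative. Its analysis is thematic, with explicit attention to disconfirming cases, and no numerical effect estimate from these girls is planned. Choosing the most affected girls is a sound way to learn about drivers and experiences. Change in participation is also measured by the survey in all Form 2 and 3 girls, which this selection leaves unbiased. All of that stands. It confines the problem to how change in the interviewed girls is interpreted, but it does not remove the problem, because the article gives assessing change as an aim and ties it to the intervention.

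Three stronger readings are tempting but not supported.

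- A reader might infer that Table 1 drops the pre-intervention interview. As step 3 of the working shows, the missing occasion is more naturally the one immediately after the intervention.
- A reader might infer that change will be measured from the survey answer used for selection. The article does not say so. If the pre-intervention interview covers a later period and serves as the reference, part of the regression will already have happened. The article states neither condition.
- A reader might infer that the interviews are bound to show improvement, or that half to three quarters of the girls would appear improved. The second figure corresponds to assumed correlations of 0.3-0.5 only. At 0.7 the model gives 36-53%, and with very stable absence the shift could be small. Nor does the article say that the interviews will be triangulated as support for an effect: its process evaluation section ties triangulation to fidelity, coverage, sustainability and acceptability.

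**Conclusion.** Both parts hold, with different certainty.

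The inconsistencies are plain on the text: 40 girls against 20, and two occasions against three, so anything from 40 to 120 interviews. Condensing a protocol into an article does not explain this, since the article prints the figures and they disagree.

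The regression-to-the-mean point follows from the stated design: selection on one high report, the same quantity asked again, change linked to the programme, and no comparator. The direction is towards apparent benefit whenever absence is not perfectly repeatable between periods. The size is unknown. About 36-78% falling below the two-day rule with no effect rests on assumed prevalences of 10-30% and correlations of 0.3-0.7. Under more stable absence the count simulation gives as little as 7%. The primary outcome and the survey part of outcome 6 are not biased by this selection. The point should be corrected, but it does not threaten the main evaluation.

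**What to change.** 1. State one number of girls per school and one interview schedule, and use them in the sampling strategy, Table 1, the outcome evaluation section and Table 2.
2. Base any statement about change in participation (outcome 6) on the full survey cohort. Keep the interviews for drivers, mechanisms and experiences.
3. In the pre-intervention interview, record days missed at the most recent period and at a usual period. Use these, not the survey answer that led to selection, as the reference for any change the girls describe.
4. Name regression to the mean as a limitation of the interview sample.

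The cost is two questions in an interview that is already planned, plus wording changes. Fieldwork changes only as far as the chosen sample size and schedule require.

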### Intervention delivery and components

The intervention will be delivered by Femme after refinement during the formative phase. The evaluation will be conducted by a MITU/LSHTM team (see figure 2). The following components are expected to be part of the finalised intervention:

**Comprehensive education sessions** will be delivered by Femme facilitators immediately following regular school activities to all Form 2 and 3 girls and boys (~500 girls and ~500 boys, age range 14–18 years) in four schools. Ideally sessions will run over 5 days and last approximately 1–2 hours per session; however, this may vary by school depending on their timetable and availability. In each school, girls and boys will first be together for two sessions covering anatomy, puberty, virginity, relationships and gender roles, basics of menstruation, reproductive health and pregnancy. Two subsequent boys’-only sessions will cover hygiene, physical (sexually transmitted infections, urinary tract infections) and mental (anxiety, substance abuse) health, gender-based violence and relationships. Three girls’-only sessions will cover hygiene, menstruation (management, reusable products), pregnancy, physical health (RTIs, STIs, UTIs), anxiety and pain management. The formative phase will inform about the frequency and distance between sessions.

**Menstrual pain management** will likely include the provision of strategies such as application of heat, dietary options, mild exercise/stretching, recommendations for over-the-counter analgesics such as Panadol or Ibuprofen, and incorporate anxiety-reducing and pain-reducing breathing techniques during the girls only sessions. During the formative phase, we will also explore (with the schools and LGAs) the best way for such analgesics to be made available and dispensed within the schools.

**Distribution of reusable menstrual products** (menstrual cups, reusable pads, period underwear). During the girls’-only sessions, students will be taught the advantages, disadvantages and usage of all products. At the end of the education sessions, girls will receive a Femme kit. If deemed appropriate during the formative phase, a boy’s kit will be developed and delivered in the pilot, such a kit could include information booklets, soap in a container, underwear.

**Two post-workshop check-in sessions** will be conducted, one at 6 weeks after the education sessions (with both boys and girls) and the other at 12 weeks (with girls only). The aim of these sessions will be to reinforce key workshop messages and support girls’ product uptake. These sessions are pivotal to reinforcing key learnings while tackling myths and misconceptions, answering questions and providing support for product usage, especially menstrual cups. Students will be guided through a quiz with specifically designed questions that will elicit conversation regarding the key topics, including: UTIs, menstrual pain management and vaginal discharge. In these sessions, Femme facilitators will identify early adopters of the menstrual cup, support them and build an encouraging support group to promote the use by others who also selected the product but may have not yet tried or have experienced challenges when first trying. Teachers will not be present during workshops or check-ins, as students will not feel free to ask pertinent and personal questions.

**Teacher/staff workshops** will take place separately in each of the four schools, before the student education sessions occur, with all teachers. They will cover the same topics as listed for the students, provide opportunities to ask questions, and female teachers will receive a reusable menstrual product. One of the secondary outcomes of the project is to improve school climate hence the involvement of boys and male teacher is an important strategy in the project. Both male and female teachers will participate in key informant interviews during formative and stakeholders’ workshops at the beginning of the intervention.

**School wash improvements** in the four schools will be based on information collected from students, teachers and districts during the formative phase and will be implemented by relevant people within each school, in partnership with Femme facilitators prior to the first workshop. Improvements are likely to include door locks, hooks on doors, soap, bins and buckets for water.

**District and school level meetings** will take place throughout the project period at suitable time points identified during the formative phase to coincide with relevant government decision-making and budgeting time points. By aligning implementation planning with government timelines, there is opportunity for intervention inclusion in annual plans, strategic plans and budgets.^23^ These meetings are intended to explore mechanisms for integration of the intervention components described above into the education system.

#### Outcome evaluation

A mixed-methods evaluation will be conducted in the four intervention delivery schools (see figure 3). The study design will be a single-arm longitudinal study with pre-post survey among students, and qualitative studies among students and staff (see table 1). For the quantitative pre-post evaluation, all girls and a subsample of 50 boys per school registered in Forms 2 and 3 will be recruited. The study population for the quantitative evaluation will comprise adolescents aged 13–18 years attending the four intervention schools.

**Figure 3 F3:**
[figure not shown]
Flow chart of the PASS MHW intervention pilot study illustrating the intervention and evaluation activities.

Qualitatively, we will conduct 20 sequential in-depth interviews at three time points (before, immediately post intervention, 12 months later) with five girls from each school, who reported in the baseline questionnaire, to have missed school for two or more days during and because of their last menstruation. The aim of these sequentialin depth interviews (IDIs) is to assess any changes in participation and to explore if/how the intervention may have impacted on the girls’ ability to participate in school. We will also conduct KIIs with two staff per school to assess MSRH knowledge among staff overseeing student’s MSRH issues while in school. All interviews and FGDs will be conducted in Swahili by a trained female research assistant accompanied by a note taker and recorded using digital voice recorders.

We will assess one primary and eight secondary outcomes. The data collection tools for each outcome are described in table 2.

**Table 2 T2:** 

Outcome	Population and method*	Proposed scale to finalise in the formative phase
**Primary outcome**		
Menstrual practices and perceptions	(1)	Menstrual Practices Needs scale.^22^ 36 questions to measure perceptions of comfort, satisfaction, adequacy, reliability and worries/concerns during the last menstrual period
**Secondary outcome**		
1. Ability to manage pain	(1)	3 questions have been drawn from Femme routine M&E tools and will be modified during the formative phase, but assess the presence and severity of pain during the last menstrual period.
2. Self efficacy of management of menstruation	(1)	Self-efficacy in Addressing Menstrual Needs Scale (SAMNS) is 26-item scale, which measures of a schoolgirl’s confidence in her capabilities to address her menstrual needs. The tool comprises 3 correlated subscales: The SAMNS comprises 3 correlated subscales: Menstrual Hygiene Preparation and Maintenance (MHPM, 17 items), Menstrual Pain Management (MPM, 5 items), and Executing Stigmatised Tasks (EST, 4 items).
3. Menstrual-related anxiety	(1)	Generalised Anxiety Disorder is a seven-item scale (GAD7) which has been translated and tested in Swahili among this population
4. Self-reported reproductive ill-health symptoms	(1)	9 questions drawn from Femme routine M&E tools to assess the presence of a series of symptoms in the last month.
5. MSRH Knowledge	(1), (2)	11 multiple choice questions have been drawn from Femme routine M&E tools and MENISCUS study in Uganda to assess knowledge of puberty in general and MSRH
6. School and social participation	(1), (3)	Quantitatively we have included 8 questions in the survey to assess participation. Qualitatively, the girls will describe experiences of their LMP including the days, activities, sessions missed at LMP because of menstruation. We will explore drivers for suboptimal participation and reasons for any changes over the course of the project.
7. School WASH facility improvements	(1), (4)	Baseline and endline checklist to capture the presence of and access to toilets, water sources, hand-washing stations and disposal methods. Questionnaire also contains eight questions to assess the availability, access and condition of WASH facilities in the school
8. School climate	(4)	Questions adopted from the Beyond Blue School Climate questionnaires.^22^ The scale has 28 items in four subscales: relationships (between students and teachers), belonging, commitment and participation.

(1) Quantitative survey of a cohort of all girls: census of all girls in Forms 2 and 3 at baseline.

(2) Quantitative survey of a cohort of 200 boys randomly selected at baseline from Forms 2 and 3.

(3) Sequential IDIs with 20 girls who (at baseline) reported to have missed two or more days of school during and because of their last menstrual period who will be interviewed at three time points.

(4) Four schools—baseline and endline assessment.

*Data sources.

WASH, water, sanitation and hygiene.

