5	National, regional and district educational authorities	Phase I: Formative Step 2: Mwanza	Observation of Femme-led meeting	~16 participants+4 Femme facilitators	No sampling as Femme will convene the meeting, the research team will be introduced at the start and state that they are there to observe the process of the meeting. No recordings or names will be taken. All workshop participants will be asked to consent to the observation.	Capture the perspectives of the participants regarding their ideas for synergies between the intervention and the current school curriculum. Understand their perceived needs, preferences and priorities for MSRH education in schools. Capture discussions around the proposed WASH and pain management components, particularly possible challenges and opposition. Using PIPA we will capture the engagement strategies applies and adopted and any successes and challenges faced.
*6*	School administrators	Phase 1: Formative Step 2: Mwanza	Observations of Femme/District led meetings	~10, 5 per school		
7	Femme facilitation team and district officials	Phase I: Formative Step 3: Mwanza	Observations of meeting	30	We will adopt a census approach and include all of the FEMME facilitators who lead the meeting and all district officials who attend.	Elicit suggestions for programme enhancements, specifically around the pain management and the involvement of the boys and WASH improvements.
8	Female and male students	Phase II: Pilot study, Mwanza	Quantitative assisted, self-completed paper-based survey conducted among a longitudinal cohort before implementation of the intervention and then 9–12 months after	~500 girls and 200 boys	All girls in Forms 2 and 3 in each school. Random sample of 50 boys per school, randomly selected from forms 2 and 3 using the school registers.	MSRH knowledge WASH facilities Menstrual needs and practices (girls only) SRH symptoms (girls only) Generalised anxiety School environment

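### Secondary outcomes 1 and 3 are named for pain-management ability and menstrual anxiety, but their stated instruments measure pain burden and general anxiety

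*Protocol article*

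**What the plan says.** Table 2 of the protocol article sets out one primary and eight secondary outcomes, each with a data source and a proposed scale.

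- **Secondary outcome 1** is "1. Ability to manage pain". Its source is the girls' survey only. Its measure is three questions from the implementing NGO's monitoring tools. These are to be modified in the formative phase, but are said to "assess the presence and severity of pain during the last menstrual period".
- **Secondary outcome 2** is self-efficacy, measured by the 26-item SAMNS. One of its three subscales is "Menstrual Pain Management (MPM, 5 items").
- **Secondary outcome 3** is "3. Menstrual-related anxiety". Its source is again the girls' survey only, and the measure is given as: "Generalised Anxiety Disorder is a seven-item scale (GAD7) which has been translated and tested in Swahili among this population".

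Table 1 (row 8, the Phase II survey) lists the survey's content as including "SRH symptoms (girls only) Generalised anxiety School environment". Under Phase I, Step 2, the list of survey sections calls the pain section simply menstrual pain, separate from self-efficacy. The theory of change (Theoretical framework) names menstrual anxiety as an element of girls' experience.

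**The concern.** An outcome's name determines the sentence written in the results. If the name and the instrument refer to different constructs, the reported conclusion is not the one the data support, however well the model is fitted.

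For outcome 1, whether pain was present and how bad it was is symptom burden. The intervention mainly teaches ways of coping with pain (The TWAWEZA programme and Intervention delivery and components). A girl may cope better with unchanged pain, or have less pain without coping any better. Presence and severity alone cannot separate these cases.

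For outcome 3, a general anxiety scale is not specific to menstruation. The design is a single-arm pre-post comparison, with 9–12 months between surveys (Table 1, row 8). General anxiety can move over that interval for many reasons, and the label would attribute the movement to menstruation.

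The first mismatch matters more. Limited pain management is one of three gaps named in the existing programme, and developing it further is part of the first specific objective. The quantitative outcome that carries its name does not measure it.

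**Working it through.** The documents give no figure to reproduce here. The check sets each label against its instrument, and then against how the rest of the article uses the terms.

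**Outcome 1**

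| Place | What it names |
|---|---|
| Table 2, label | Ability to manage pain |
| Table 2, instrument | Presence and severity of pain, three questions |
| Phase I, Step 2, survey sections | Menstrual pain |
| Table 1, row 15 (interviews with 20 girls) | Ability to manage pain, as a topic in its own right |
| Table 2, outcome 2 | A five-item pain-management subscale |

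The article therefore treats pain and the management of pain as distinct. The three questions fall on the pain side and the label on the management side.

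**Outcome 3**

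| Place | What it names |
|---|---|
| Table 2, label | Menstrual-related anxiety |
| Table 2, instrument | GAD-7 |
| Table 1, row 8 | Generalised anxiety |
| Theoretical framework | Menstrual anxiety |

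Table 1, row 8 covers about 500 girls and 200 boys. It marks menstrual needs and SRH symptoms as girls only, but leaves generalised anxiety unmarked. That fits a general construct rather than a menstrual one.

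**Where closer measures already sit**

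- *Pain management.* The SAMNS subscales have 17 + 5 + 4 = 26 items, so pain management is 5/26 ≈ 19% of the scale. The article does not say how the SAMNS is scored. Assume the total is an equally weighted item mean. Then a shift of d per item confined to the pain subscale moves the total by (5/26) × d ≈ 0.19d. The signal is in the data, but it is diluted if only the total is reported.
- *Menstrual worry.* The MPNS-36 under the primary outcome includes items on worries and concerns in the last period. These are menstruation-specific, but they are one part of a scale about practice needs.

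**Extent.** 2 of 8 secondary outcomes (25%) are affected. The sample size calculation uses the MPNS-36 alone, and the primary model is for the MPNS, so neither is touched.

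**The case against.** The strongest case on the other side has four parts.

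1. **The scales are provisional.** Table 2 heads the column as proposals to be settled in the formative phase, and the article expects that phase to be over by publication. Final items may stand in a document not shown here. This weakens the pain half but does not remove it: the row leaves the wording of the questions open while still stating what they assess. No change is signalled for the GAD-7.
2. **Construct fit is itself under study.** The strengths list says that several outcomes and triangulation will help show whether the right constructs are being measured. That is a reasonable pilot aim, but it does not make a label correct when its own row contradicts it.
3. **The anxiety row is transparent.** The GAD-7 is named beside the label, so a careful reader can see what was used. This limits the harm, but a results summary that carries only the label would lose that protection.
4. **These are secondary outcomes in a pilot.** True, and it bounds the importance.

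A reader might also infer more than the documents support:

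- *That a real gain in pain management would be missed.* It could still show in the SAMNS pain subscale and in the interviews. It would be filed under another heading, not lost.
- *That a milder period would be scored as better ability.* No scoring rule is given and the three questions are not shown.
- *That the SAMNS subscale measures ability itself.* Table 2 describes the SAMNS as a measure of confidence, so it supports a claim about perceived ability only.
- *That the MPNS worry items could replace the GAD-7 as a measure of menstrual anxiety.* They are a partial proxy.
- *That correct names would make the changes attributable to the intervention.* The article concedes there is no control group, and any time trend remains under any name.

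**Conclusion.** The point holds for both outcomes on the article's own wording. Each row of Table 2 pairs a label with an instrument for a different construct, and Table 1 and the list of survey sections use the instrument's construct, not the label's. If the plan is followed as written, symptom burden is reported as management ability, and general anxiety as menstrual anxiety.

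The error lies in what the estimates mean, so it cannot be expressed as a loss of power or a bias of known size. The conclusion assumes that the final pain questions keep the target stated in Table 2 and that the GAD-7 is retained. If the finalised survey replaced either, that half of the point would need to be looked at again. The change is worth making because it alters what may be concluded about a gap the study aims to close, at very little cost.

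**What to change.** - **Outcome 1:** rename it *presence and severity of menstrual pain*.
- **Perceived ability to manage pain:** report the SAMNS pain-management subscale separately under this name, as a self-efficacy measure. State that its five items also count towards the SAMNS total in outcome 2, so the two results are not independent.
- **Interviews:** list them (source 3 in Table 2) as supporting evidence on pain management. Table 1 already gives them that topic, and Table 2 already credits them for outcome 6.
- **Outcome 3:** rename it *generalised anxiety symptoms (GAD-7)* and make no menstrual-anxiety claim from it. If menstrual worry is discussed, use the MPNS worry and concern items and describe them as partial and supportive.
- **Interpretation:** keep the existing caution about the missing control group for both renamed outcomes.

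The cost is a change of wording in Table 2 and one extra reported subscale. All the items and interviews are already planned, so no new data are needed. The one drawback is the overlap between the pain subscale and outcome 2, which disclosure handles.
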